#### Foot mechanics

Foot mechanical outcomes will consist of dynamic arch index (dAI), static arch height index (sAHI) whilst sitting and standing (double limb support), foot and arch height pliability ratios, hallux angle, and footstrike pattern while jogging and running.

The dAI describes the proportion of the middle third of a footprint compared to the whole footprint area (except for the toes) and was firstly described by Cavanagh and Rodgers [27] (Fig. 2). This method was shown to be valid and reliable in children [28, 29]. The dynamic footprints geometric will be acquired with a capacitance-based pressure platform system (Emed n50, Novel GmbH, Munich, Germany) using a two-step protocol [29, 30]. The platform has 6080 sensors in an area of 47,5 × 32 cm (4 sensors/cm^2^) and has been shown to be reliable in adult [31] and paediatric populations [29]. In order to level the platform to the ground, it will be embedded in a 300 cm wooden walkway.

**Fig. 2 Fig2:**
[figure not shown]
Example of a digital footprint with masking into forefoot, midfoot and hindfoot region for calculation of the dynamic arch index according to Cavanagh and Rodgers (1987)

Footprint data will be used to calculate the hallux angle according to R Donatelli and SL Wolf [32].

Measures of static foot anthropometrical data will be obtained with a specially constructed caliper (Fig. 3). This caliper consists of heel cups for the placement of both feet and sliding indicators for proper measurement of heel-to-toe length (HTL), foot width (FW) and dorsum height. HTL will be defined as the distance from the most posterior aspect of the foot to the most anterior part of the toes. Dorsum height will be measured at 50 % of HTL and the static arch height index (sAHI) will be defined as the ratio of dorsum height and HTL:

**Fig. 3 Fig3:**
[figure not shown]
Heel to toe length, foot width and dorsum height measurements will be obtained using a specially constructed platform. Dorsum height will be measured at 50 % of the heel to toe length using the sliding caliper pictured on the right foot in this picture. Static arch height index will be defined as the ratio of dorsum height and heel to toe length

$$ Static\  arch\  height\  index = \frac{Dorsum\  height}{Heel-to- toe\  length} $$

Feet of the participants will be measured at sitting (10 % of body weight (BW)) and standing (50 % of BW) and the pliability ratio will be calculated according to Kadambande et al. [20]:$$ Pliability\  ratio = \frac{HTL\ 50\%\  of\ BW \times FW\ 50\%\  of\ BW}{HTL\ 10\%\  of\ BW \times FW\ 10\%\  of\ BW} $$

Foot strike patterns will be captured during 20 m jogging and both sprinting trials in each condition at the 17.5 m mark using a wide-angle high speed camera (GoPro HD Hero 4, GoPro Inc., San Mateo, California, USA). The camera will be positioned 150 cm from the midline orthogonal to the marked running way and set to record 120 frames per second at a resolution of 1280 × 720 pixels. After testing, videos will be processed using a video editing software (Adobe Premiere Pro CS 6, Adobe Systems, San Jose, California, USA) and rated independently by two reviewers, with a third experienced reviewer for consensus. A rearfoot strike is defined as a first ground contact with the heel or the rear third of the foot, while a forefoot strike is present when the anterior part of the foot first contacts the ground. For a midfoot strike heel and anterior part of the foot contact the ground simultaneously. This method has been used successfully in other studies to determine the foot strike pattern [33].

#### Motor performance

Participants will complete multiple tests to assess motor performance; 20 m sprint [34], lateral jumping, standing long jump, and backwards balancing [35]. Each station will be performed in two conditions: barefoot and wearing sport shoes.

Preceding the lateral jumping (Additional file 3), participants will stand in one half of a square next to a line, indicated on the floor by masking tape. He/she will be instructed to jump sideways as fast as possible for 15 s. One minute rest will be given between the two trials per condition and the average score of each condition will be used for analysis. For the standing long jump (Additional file 4), a participant will be instructed to stand with their toes adjacent to a labelled start line, bend at the knees whilst swinging the arms backwards and subsequently, jump as far as possible on to a soft rebounding mat. One of the researchers will place a rod at the most posterior of where the participant landed and will read off the distance on the measuring tape attached parallel to the rebound mat on the floor. This will be repeated three times per condition and the distance of the best trial per condition is used for analysis. A sprinting lane of 20 m (Additional file 5) will be indicated on the floor by a start line labelled by tape and two pylons at 0, 10 and 20 m, as well as one meter after the 20 m mark as a dummy. A time sensor device will be placed at the start, 10 and 20 m. In Germany mobile magnetic timing gates from Humotion SmarTracks (Münster, Germany) will be used and Brower Timing Systems speed gates (Salt Lake City, UT, USA) in South Africa. The 10 m and 20 m time of the best trial per condition will be used for analysis. Lastly participants will be asked to walk backwards (Additional file 6) over a 6 cm, 4.5 cm and 3 cm wide balance beams with, respectively, 2 trials per beam [35]. The first step after the starting position will not be counted, every subsequent step will then be counted until one foot touches the ground or a maximum of 8 steps per beam is achieved. The children will be instructed to look up straight (with an X on eye level) and put their next step directly behind the other foot. The scores of two trials on each of the three beams will be added to a total score per condition for analysis (max 48 points).

### Data collection and management

Data will primarily be collected on paper sheets and then transferred to electronic spreadsheets at each testing site (Germany and South Africa). The entered data will be checked by the principal investigators. The pedobarographic data will be collected within the provided software (Novel database pro m, Version 24.3.20, Novel GmbH, Munich, Germany) and then exported as ASCII files and included into the spreadsheet. Electronic data will not include any confidential participant information and will then be transferred via secure servers to Germany for further processing and statistical analysis. As specified in the ethically approved data protection declaration for the participants, the encoded data will be stored on external hard disks in a locked safety cabinet for 10 years. Participants have the right to obtain the personalised data. Data analysis and publication will only be done in an anonymised format.

### Sample size

Although we did not opt to distinguish primary or secondary outcome measures, the dAI was used to enable a sample size calculation. Muller et al. [36] has shown that the average dynamic arch index (μ: 0,19) and the accompanying standard deviation (SD: 0065) are stable between the ages of 6 and 13. The minimal important difference was set at 20 % of the average (0.19; i.e., 0.038). With a two-sided significance level of 0.05, and assuming a power of 0.8, a minimum of 16 participants per age group, per country, had to be included for this study. Due to the diversity of the study, additional power calculations have been performed. Based on the arch height ratio derived from Waseda et al. [22] the sample size for arch height ratio (navicular height*100/foot length) should be *n* = 12 per age group (μ = 15,0; SD = 2,6). Furthermore, based on a preliminary study on children, the sample size based on the standing long jump should be *n* = 18 (μ = 152,9; SD = 31,5), for lateral jumping *n* = 22 (μ = 38; SD = 9,2) and for 20 m sprint *n* = 12 (μ = 3,81; SD = 0,64). Therefore, our *n* = 20 per group seems to be sufficient. In order to allow for these differences and other unknown variances within the other variables we choose to increase the number from 16 to 20 participants per age group, per country.

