The aim of our study is to evaluate the effect of being habitually barefoot on foot mechanics and motor performance of children and adolescents between the ages of 6–18 years. Additionally, we will evaluate if differences between habitually barefoot and shod children are age-dependent. Based on current knowledge, we hypothesize that children growing up wearing shoes regularly, have lower arches compared to their barefoot counterparts. It is also anticipated that the habitually barefoot children perform better on the barefoot motor performance tasks than the habitually shod children.

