### Statistical analysis

Descriptive data will be presented using descriptive statistics. The participant’s barefoot questionnaire and the PAQ outcomes will be compared to all attending children in 2 primary (1 rural, 1 urban) and 2 secondary schools to assess external validity. The outcome measures will be evaluated for normality using Shapiro-Wilkins and visually using P-P plots, if possible, non-normal distributed data will be adjusted. Mixed Models linear regression will be used to assess if the foot mechanical and motor performance outcomes differ between the barefoot and the shod participants (fixed factors). Furthermore, we will test differences due to being barefoot or shod change by age by adding an interaction of age*group to the linear regression. Differences in foot strike pattern during jogging and sprinting between barefoot and shod participants will be assessed using ordinal regression. The school of a participant will be added to the model as a random effect in order to adjust for possible differences between the schools and their geographical location. Furthermore, Gender, BMI, PAQ-Score, ethnicity and inside/outside testing will be tested for confounding in all models (regression coefficient changes >10 %). We hypothesize that older boys could have higher arches (lower dAI) [37] and perform better on motor performance tasks, while girls’ feet will show a higher pliability. BMI increases the dAI and possibly decreases motor performance [38, 39]. A higher level of physical activity (higher PAQ score) is probably related to better motor performance. And lastly, Caucasians could have higher arches (lower dAI) [40].

We anticipate that gender might modify the effect of being barefoot or shod on the outcome measures and therefore gender will additionally tested as an effect modifier (interaction between outcome and gender *p* < 0.1). In all cases, a significance level of 5 % is pre-stipulated.

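### The stated 80% power is not the power of either planned test (pooled group effect, age-by-group term), and on the printed dAI inputs it does not hold for the within-age comparison either

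*Protocol article*

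**What the plan says.** **Sizing (Sample size).** No primary outcome is named, but "the dAI was used to enable a sample size calculation". The inputs are "the average dynamic arch index (μ: 0,19", "the accompanying standard deviation (SD: 0065) are stable between the ages of 6 and 13" and "The minimal important difference was set at 20 % of the average (0.19; i.e., 0.038". The error rates are set by "With a two-sided significance level of 0.05, and assuming a power of 0.8". The result is that "a minimum of 16 participants per age group, per country, had to be included for this study", and this is then raised to 20. The Abstract gives a total of 520 for ages 6 to 18. Since 20 × 2 countries × 13 = 520, an age group is a single year of age.

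**Analysis (Statistical analysis).** A mixed linear model compares barefoot with shod participants across all ages, with school as a random effect. Age dependence is then tested by "adding an interaction of age*group to the linear regression". No test within one age year is described.

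**Aims (Background).** Beyond the main comparison, "we will evaluate if differences between habitually barefoot and shod children are age-dependent". No target effect or power is given for this.

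**The concern.** The power statement describes one comparison and the analysis makes two others. A reader who sees a study stratified by year of age with 80% power may assume that the figure covers the age-dependence aim. A non-significant interaction could then be taken as evidence that the barefoot–shod difference is the same at all ages, when nobody has stated what change the test can detect. Conversely, the pooled comparison has far more power than the section conveys.

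The figure also needs checking in its own right. If 80% is wrong even for the within-age comparison, it describes no test at all.

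**Working it through.** **1. Inputs.** From Sample size: mean dAI 0.19, difference 0.038, two-sided α = 0.05, power 0.80, 20 per age year and country. The SD is printed as 0065; I read it as 0.065, assuming a lost decimal mark. From the Abstract: ages 6 to 18, so 13 age years.

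**2. The plan's own figure.** Two-sample comparison in one age year: n per cell = 2 × (1.96 + 0.84)² / (0.038/0.065)².
- The standardised difference is 0.585, which gives 46 by the normal formula and 47 by the t-test. The stated 16 is not reproduced.
- Power by t-test is 0.36 with 16 per cell and 0.44 with 20 (normal approximation 0.38 and 0.46).
- Other forms do not give 16 either: one-sided two-sample 37, two-sided one-sample 23 to 25, one-sided one-sample 19.
- Sixteen per cell gives 80% only if the SD is about 0.037 to 0.038, or the difference about 0.064.

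The same two-sample formula with a 20% difference comes close to the section's other four sizes. The 20% is stated only for dAI; I assume that it was used throughout.

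| Outcome | Stated n | Recomputed (normal / t) |
|---|---|---|
| Arch height ratio | 12 | 12 / 13 |
| Standing long jump | 18 | 17 / 18 |
| Lateral jumping | 22 | 24 / 25 |
| 20 m sprint | 12 | 12 / 13 |

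So the intended calculation is a within-age two-sample comparison, and the dAI figure is the clear outlier.

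**3. Pooled group effect.** Assume 13 × 20 = 260 barefoot and 260 shod.
- Detectable difference at 80% power: 2.80 × √(2/260) = 0.246 SD, or 0.016 for dAI.
- Power at 0.038 is above 0.99. At an assumed design effect of 3 for school it is still 0.97.

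**4. Age-by-group term.** Assume linear age and independent children.
- Sum of (age − 12)² over ages 6 to 18 = 182; × 20 = 3640 per group.
- SE of the slope difference = SD × √(2/3640) = 0.0234 SD per year; over 12 years, 0.281 SD.
- Change detectable with 80% power: 2.80 × 0.281 SD = 0.79 SD, or 0.051 for dAI at SD 0.065.
- Power = Φ(total change / (0.281 × SD) − 1.96).

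| Total change in dAI difference, ages 6–18 | Power, SD 0.065 |
|---|---|
| 0.019 | 0.18 |
| 0.038 | 0.55 |
| 0.057 | 0.88 |
| 0.076 | 0.99 |

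**5. Sensitivity of the 0.55.**
- Assumed design effect of 1.5 to 2: 0.40 to 0.31.
- SD near 0.037, the value at which 16 per cell would be right: about 0.95.
- Age as 13 categories (12 df), same linear trend: 0.21.
- A step of 0.038 between ages 12 and 13, still tested with linear age: 0.82.

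**6. Other sized outcomes.** For a total change of 20% of the mean, with the printed SDs, interaction power is 0.84 (lateral jumping), 0.93 (long jump), 0.98 (arch height ratio) and 0.99 (sprint).

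**The case against.** A reader might infer that the age aim has 55% power at the protocol's own minimal important difference, against a promised 80%. The documents do not support that, for three reasons.

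- The protocol defines 0.038 as a difference in means. It does not define it as the amount by which that difference must change between ages 6 and 18. That target is an assumption of this review, and power runs from 0.18 to 0.99 over plausible alternatives.
- The two figures cannot both hold. At SD 0.065 the interaction has 55%, but the within-age 80% is then false. At an SD near 0.037 the 80% is true, but the interaction has about 95%. The contrast arises from the unresolved dAI input, not from the choice of test.
- It singles out one outcome. No outcome is primary, and the other four sized outcomes have 0.84 to 0.99 on the same basis.

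It can also be said that age dependence is an additional aim that need not carry its own power, that the article never attaches 80% to it, and that rules for reporting the interaction may properly sit in an analysis plan that is not shown.

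All of this stands, and it limits the point. It does not remove it. The article does print a power figure; the comparison it belongs to is not in the stated analysis, and the figure does not follow from its printed inputs. Those are statements in the document, not omissions from it.

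**Conclusion.** The point holds in a limited form. The 80% is stated for a comparison within one age year that the analysis section does not include, and it is the power of neither planned test. On the printed dAI inputs it is not correct for the within-age comparison either: about 36% with 16 per cell and 44% with 20, with about 47 needed. This rests on reading 0065 as 0.065.

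The main comparison is not in doubt. With about 260 per group its power at 0.038 exceeds 99%. The equal split is itself an assumption, because the study is sized by country while barefoot status comes from a questionnaire.

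For the age-by-group term no single power figure can be assigned to the design. The 0.55 applies only to a total change of 0.038, SD 0.065, linear age and no clustering by school. Any shortfall concerns dAI. It would be wrong to conclude that the study as a whole is underpowered, or that the age aim is underpowered for every outcome.

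**What to change.** In Sample size:

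1. Reconcile the dAI SD with the 16 first. State the intended SD and recompute, because every dAI figure below depends on it.
2. Replace the per-age power claim with figures for the two planned tests.
   - Pooled effect: detectable difference about 0.25 SD with 260 per group, before allowing for school.
   - Age-by-group term: state the target change over ages 6 to 18, the coding of age and the resulting power. Under linear age and independence the change detectable with 80% power is about 0.79 SD (0.051 for dAI at SD 0.065). Give the range in the working above, and say that school clustering lowers these values.

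In Statistical analysis, add one sentence: the age-by-group estimate is reported with its 95% confidence interval, and a non-significant term is not read as absence of age dependence.

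The cost is a rewritten paragraph and one added sentence, with no further enrolment or data. The drawback is that the stated power for dAI will look less favourable.

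### The dynamic arch index sample size does not follow from its own inputs: they require 46 to 47 children per group at each age, not 16, so 20 per cell gives about 44% power where 80% is claimed

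*Protocol article*

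**What the plan says.** The Sample size section of the protocol article names no primary outcome but uses the dynamic arch index to size the study. It takes from a cited study "the average dynamic arch index (μ: 0,19") and "the accompanying standard deviation (SD: 0065"). The target is then fixed: "The minimal important difference was set at 20 % of the average (0.19; i.e., 0.038"). The error rates are given as "With a two-sided significance level of 0.05" and "assuming a power of 0.8". From these it concludes that "a minimum of 16 participants per age group, per country, had to be included for this study".

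The section adds requirements for four other outcomes: 12 for arch height ratio, 18 for standing long jump, 22 for lateral jumping and 12 for the 20 m sprint. It then states that n = "20 per group seems to be sufficient" and raises 16 to 20 per age group per country, as an allowance for variation in the other variables. Twenty children in each of 13 one-year age groups (6 to 18) in two countries gives the 520 in the Abstract.

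The Statistical analysis section plans a mixed linear model with barefoot or shod as a fixed factor, school as a random effect, and an added age-by-group interaction. It plans no separate test at each age.

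**The concern.** All inputs for the dynamic arch index are printed, so the figure can be checked directly, and 16 is about a third of what they require. This is the outcome on which the total of 520 rests. The increase to 20 is presented as a margin, but it is less than half of the calculated need.

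Separately, and without any recalculation, a stated requirement of 22 cannot be met by 20.

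At stake is the power claim itself. It is made per age group, and age-dependence is one of the study's two questions. A reader who believes that each age has 80% power for a 20% difference would read too much into an absent difference at a given age. The power of the analysis that is actually planned is not stated in the section.

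**Working it through.** **Inputs (Sample size section).** Mean 0.19; SD 0.065 (printed without its decimal mark); difference 0.038 = 0.20 × 0.19; two-sided 5%; power 0.8; two equal independent groups within one age.

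**1. The plan's figure.** n per group = 2(1.96 + 0.8416)² × (SD/difference)² = 15.70 × (0.065/0.038)² = 15.70 × 2.926 = 45.9, so 46. The t-test version gives 46.9, so 47. The stated 16 is not reproduced.

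**2. Could another reading give 16?**

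| Variant at 80% power | n |
|---|---|
| One-sided, two groups | 37 |
| One-sample or paired, two-sided | 23 (normal), 25 (t) |
| One-sample or paired, one-sided | 19 (normal), 20 (t) |
| SD 0.0065, two groups (normal) | 1 |

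None does. Sixteen corresponds to a difference of about one SD (15.70 × 1² = 15.7), whereas the stated difference is 0.038/0.065 = 0.585 SD. It would follow from an SD of about 0.037 to 0.038, or from a difference of about 0.064 to 0.067.

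**3. Power at the stated sizes (t test, 0.585 SD).** n = 16: 36%. n = 20: 44%. The normal approximation gives 38% and 46%. With 20 per group, 80% power needs 0.909 SD = 0.909 × 0.065 = 0.059, and 0.059/0.19 = 31% of the mean.

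**4. The other outcomes.** The article states the 20% rule only for the dynamic arch index. Extending it to the others is an inference.

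| Outcome | Difference/SD | Normal | t | Stated |
|---|---|---|---|---|
| Arch height ratio | 3.0/2.6 | 11.8 | 12.8 | 12 |
| Standing long jump | 30.58/31.5 | 16.7 | 17.7 | 18 |
| Lateral jumping | 7.6/9.2 | 23.0 | 24.0 | 22 |
| 20 m sprint | 0.762/0.64 | 11.1 | 12.1 | 12 |

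All four stated figures lie within about two children of these results, although no single formula with one rounding rule gives all of them. The method is therefore plausible, and the dynamic arch index is the large outlier (16 against 46 to 47). Lateral jumping is also slightly low. Under the 20% rule its power at 20 is 72%; taking the article's own 22 as correct for 80% power, it is about 76%.

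**5. The planned pooled contrast.** Take 13 × 20 = 260 per group, with country standing in for barefoot or shod. SE = 0.065 × √(2 × DE/260), where DE = 1 + (m − 1) × ICC is the design effect. Neither m nor the ICC is in the article; I assume m = 26 children per school and vary the ICC.

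| Assumed ICC | DE | SE | Power for 0.038 |
|---|---|---|---|
| 0 | 1.00 | 0.0057 | >99% |
| 0.01 | 1.25 | 0.0064 | >99% |
| 0.05 | 2.25 | 0.0086 | 99% |
| 0.10 | 3.50 | 0.0107 | 95% |
| 0.20 | 6.00 | 0.0140 | 78% |

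For the third row: 0.038/0.00855 = 4.44, and 4.44 − 1.96 = 2.48, which gives 99%. These are normal approximations without covariate adjustment.

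**6. The interaction, for orientation.** With age linear and 20 per cell, the variance of age over 13 equally filled years is (13² − 1)/12 = 14. Ignoring clustering, the detectable difference in slope is 2.80 × 0.065 × √(2/(260 × 14)) = 0.0043 per year. Over the 12 years from 6 to 18, this is a change of about 0.051 in the group difference.

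**The case against.** The strongest reply has three parts.

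First, the SD is visibly misprinted and comes from a source not at hand. If the source value were about 0.037, 16 would be right and the printed SD wrong. This stands as a reason to check the source before editing. It does not rescue the paragraph: 0.065 is the natural reading beside a mean of 0.19, 0.0065 does not give 16 either, and under any reading something printed there needs correcting.

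Second, the planned analysis pools the ages, so the shortfall within one age does not carry over to the main contrast. This also stands. A reader might infer that the study as a whole has 44% power, or that it needs 46 to 47 per cell, which would be 1,196 to 1,222 children (46 or 47 × 26 cells). The document does not support that: no age-by-age tests are planned, and the pooled contrast has ample power for 0.038 under moderate clustering. The 44% describes only the comparison within one age, which is the unit the article chose for its own calculation.

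Third, a reader might infer that the dynamic arch index is the only figure in error and that the rest reproduce exactly. That is too strong. Lateral jumping is also a little low, the match for the others depends on the formula and rounding, and the 72% for lateral jumping depends on extending the 20% rule. The conflict between 22 and 20 needs no such assumption.

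**Conclusion.** The point holds as an error in the stated sizing rationale and in the per-age power. With the SD read as 0.065, the requirement is understated almost threefold (16 against 46 to 47), and power at 20 per cell is about 44% instead of 80%. The internal conflict over lateral jumping is certain but small.

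The size of the main error rests on the reading of the SD; the disagreement between the printed inputs and 16 does not. Nothing here shows that the pooled barefoot-versus-shod analysis is underpowered. Its power for 0.038 is about 99% at a design effect of 2.25. That figure takes country as a stand-in for the questionnaire-defined groups and assumes the clustering; power falls below 80% only towards an ICC of 0.20 with 26 children per school.

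The correction should be made, because the only stated justification for the sample size is wrong as written and is cheap to restate.

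**What to change.** Keep 520 children and reword the Sample size paragraph.

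1. Check the SD of the dynamic arch index against its source and print it with its decimal mark.
2. If it is 0.065, replace 16 with 46 to 47. State that 20 per age group per country gives about 44% power for 0.038, and 80% power only for about 0.059 (31% of the mean). If it is another value, correct the printed SD and recompute.
3. Delete the statement that 20 per group is sufficient, and state plainly that 20 is below the article's own 22 for lateral jumping.
4. Rest the justification on the planned model. Give power for the pooled contrast over a range of school clustering and for the expected numbers of barefoot and shod children, and give the detectable age-by-group interaction on the same basis.
5. Do not claim 80% power within single age groups.

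The cost is one paragraph and one look at the cited source. No further recruitment follows, but the stated per-age power becomes less favourable.

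### The plan calls 20 per age group per country sufficient, but its own lateral-jumping figure is 22; within an age group that outcome has about 72-76% power

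*Protocol article*

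**What the plan says.** The Sample size section first sizes the study on the dAI. The difference is given as "The minimal important difference was set at 20 % of the average (0.19; i.e., 0.038", and the error rates as "With a two-sided significance level of 0.05, and assuming a power of 0.8". This leads to 16 per age group and country.

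Additional calculations follow, each printed with a mean, an SD and a required number, but without the difference to be detected:

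- arch height ratio: 12 (mean 15.0, SD 2.6)
- standing long jump: "the sample size based on the standing long jump should be *n* = 18 (μ = 152,9; SD = 31,5"
- lateral jumping: "for lateral jumping *n* = 22 (μ = 38; SD = 9,2"
- sprint: "for 20 m sprint *n* = 12 (μ = 3,81; SD = 0,64"

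The next sentence is "Therefore, our *n* = 20 per group seems to be sufficient". The section then raises the number from 16 to 20 per age group and country, which matches the total of 520 in the Abstract (20 × 13 year groups × 2 countries).

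**The concern.** The conclusion is introduced as following from the listed figures, yet one of them, 22, is larger than 20. The section neither acknowledges nor explains the exception, and no other part of the article does so.

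The section declines to rank outcomes as primary or secondary, so lateral jumping cannot be set aside as a lesser measure. Whether differences depend on age is a stated aim (end of Background, and Discussion). Someone who looks at lateral jumping at a particular age, and relies on the sufficiency sentence, would credit that comparison with 80% power when it has less.

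**Working it through.** **Step 1. The printed contradiction.** Required for lateral jumping: 22. Planned: 20. This needs no assumption.

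**Step 2. Power at 20 from the plan's own 22.** Suppose 22 per group gives exactly 80% power at two-sided 5%. The standardised signal at 22 is then 1.960 + 0.842 = 2.802. At 20 it is 2.802 × √(20/22) = 2.671. Power is Φ(2.671 − 1.960) = Φ(0.711) = 76%. The t-test version also gives 76%.

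**Step 3. Which difference lies behind the additional figures?** None is printed. As an assumption, take the dAI rule (20% of the mean) with two-sided 5% and 80% power, two independent groups, and n per group = 2(1.960 + 0.842)² / d², where d = 0.20 × mean / SD.

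| Outcome | d | Normal approx. (raw) | t test (raw) | Printed |
|---|---|---|---|---|
| Arch height ratio | 3.0/2.6 = 1.154 | 11.8 | 12.8 | 12 |
| Standing long jump | 30.58/31.5 = 0.971 | 16.7 | 17.7 | 18 |
| 20 m sprint | 0.762/0.64 = 1.191 | 11.1 | 12.1 | 12 |
| Lateral jumping | 7.6/9.2 = 0.826 | 23.0 | 24.0 | 22 |

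Rounded up, the first three come to 12-13, 17-18 and 12-13, within one child of the printed values. The rule is therefore a plausible reading, though no single convention gives all the printed numbers: 18 fits the t test, and the two 12s fit the normal approximation. For lateral jumping the raw values are 23.003 and 24.002, so 23-24 by normal approximation and 25 by t test when rounded up strictly. The printed 22 is one below the raw normal value. A one-sided test would need only 19, so it does not explain 22 either.

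**Step 4. Power at 20 per group under the 20% assumption.**

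- Lateral jumping, normal approximation: 0.826 × √(20/2) = 2.612; Φ(2.612 − 1.960) = 74.3%. By t test: 72.1%.
- Arch height ratio: 95.4% (normal), 94.5% (t).
- Standing long jump: 86.7% (normal), 84.9% (t).
- 20 m sprint: 96.5% (normal), 95.6% (t).

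**Step 5. Difference detectable in lateral jumping with 80% power at 20 per group.** Normal approximation: 9.2 × 2.802 × √(2/20) = 8.2 jumps, or 8.2/38 = 21% of the mean. By t test: about 8.4 jumps, or 22%. Under the 20% rule the target is 7.6.

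**Step 6. The pooled comparison.** With 520/2 = 260 per country and d = 0.826, power is effectively 100%, ignoring school clustering and taking country as the barefoot-shod split.

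**The case against.** **The planned analysis is not one test per year of age.** The Statistical analysis section specifies a mixed model over all participants, with an age-by-group interaction and school as a random effect. The motor-performance hypothesis in the Background is stated for barefoot and shod children overall. A reader might infer that about a quarter of true differences would be missed in the test of that hypothesis. The documents do not support this, as Step 6 shows. What survives is narrower: the section chose the single age group as its sizing unit, and its statement is wrong in that frame.

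**No difference is stated for lateral jumping.** This is correct. The 20% rule is given for the dAI only, so 72-74% and 23-25 rest on an inference. A reader might conclude that 22 is an error that should read 25. The text does not fix a convention that would settle this, and 22 is within one of the normal-approximation value. The comparison of 20 with 22, and the 76% derived from it, do not need the 20% rule.

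**The SD may be too large for a single age group.** The article says only that it comes from a preliminary study on children. If that sample mixed ages, the within-age SD could be smaller. At an SD of about 8.4-8.6, 20 per group would reach 80% for 7.6 jumps. This is possible, but the article does not say so, and it offers 9.2 as the planning value.

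**The sentence is hedged.** It says only that 20 seems enough. It is still drawn as a conclusion from a list that contradicts it for one outcome.

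**Lateral jumping may not be the only shortfall.** A reader might infer that 20 is adequate for everything else. That does not follow. Reading the printed dAI SD (0065) as 0.065, the stated difference of 0.038 needs 46-47 per group, and 20 gives about 44-46% power. That is a separate matter, but replacement text must not imply that the dAI is covered.

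**Conclusion.** The sufficiency statement is wrong for lateral jumping on the plan's own figure. Within one age group the shortfall is 2 to 5 children per group, or about 4 to 8 percentage points of power: 76% if 22 is taken as exactly 80%, and 72-74% if a 20% difference is assumed. All these figures assume two independent groups of equal size, two-sided 5% and, for the lower range, the printed SD of 9.2. The point bears on what is said about single age groups, not on the pooled test, and it gives no reason to enlarge the study.

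**What to change.** Replace the sufficiency sentence with a statement along these lines: under an independent-sample calculation at two-sided 5%, and assuming a difference of 20% of the mean, 20 children per age group and country give about 94-95% power for arch height ratio, 85-87% for standing long jump and 96% for 20 m sprint, but only about 72-76% for lateral jumping within an age group. The upper end of that last range takes the printed 22 as exactly 80%.

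Print the difference and formula used for each outcome. Restate the lateral-jumping requirement to match: 23-24 by normal approximation or 25 by t test. If a difference other than 20% was intended, give it and recompute. Note that these figures apply to single age groups, and that the overall comparison uses the pooled mixed model. Make no claim of sufficiency for the dAI until its calculation has been checked.

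The cost is the wording of one paragraph and a less favourable stated power for lateral jumping. Enrolment and the planned analysis stay as they are.
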